**Methods/design:**

This is a multicenter randomized controlled clinical trial. According to the ratio of 1:1:1, 90 patients with irritable bowel syndrome will be randomly divided into specific acupoints (SA) group, non-specific acupoints (NSA) group, and non-acupoints (NA) group. All patients will be treated with acupuncture 12 times within 4 weeks and followed up for 8 weeks. The primary outcome is the response rate, the percentage of patients whose average value of worst abdominal pain is 30% better and the days of loose stool is 50% less than the baseline, at week 4 after randomization. The secondary outcomes include the response rates at other time points, IBS Symptom Severity Scale (IBS-SSS), Patient Health Questionnaire-9 depression scale (PHQ-9), IBS-Quality of Life scale (IBS-QOL), IBS Adequate Relief (IBS-AR), Abdominal Pain Score, Abdominal Bloating Score, Bristol Stool Score (BBS), blinding assessment, and credibility evaluation. Adverse events will be monitored and recorded during the trial.

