### Outcomes

#### Primary outcome

In this trial, the response rate defined as the percentage of patients whose average value of worst abdominal pain is 30% better and the days of loose stool is 50% less than the baseline. The primary outcome is the response rate of week 4 after randomization. Patients will be asked to record daily IBS symptoms, including worst abdominal pain and stool type through Bristol Stool Scale. The score of worst abdominal pain in the preceding 24 h will be evaluated by visual analog scale (VAS), and the average value of worst abdominal pain will be calculated weekly.

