#### Secondary outcomes

##### The response rates at other time points

The response rate will also be measured at weeks 1, 2, 3, 8, and 12 after randomization.

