### Analytical methods

In this study, statisticians who blind to the group assignment will perform analyses using SPSS 22.0 statistical software. Continuous data will be represented by mean ± standard deviation (M ± SD) or median combined with interquartile range, whereas categorical data will be represented by frequency, constituent ratio, and percentage. Student’s *t* test or Wilcoxon rank-sum test will be used for the comparison of continuous variables, and chi-square test or Wilcoxon rank-sum test will be used for the comparison of categorical variables. *P* < 0.05 is considered to indicate statistical significance. Intention-to-treat (ITT) set will be used in all efficacy analysis, which will consist of all patients who have been randomized into groups, and the missing outcome data will be complemented using last observation carried forward (LOCF) or multiple imputation.

For the primary outcome, covariate analysis will be conducted applying a logistic regression model that includes baseline covariates for both pain score and stool consistency. A per-protocol analysis will be used for primary outcome as sensitivity analysis covering patients who complete ≥ 10 sessions and have no major protocol violations (taking other drugs during the trial, etc.).

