## Discussion

IBS is one of the most common functional gastrointestinal diseases and causes a considerable financial burden for individuals and society [10, 29]. This trial will evaluate the efficacy of SA versus NSA and NA in improving the symptoms of IBS. In this trial, we optimized the study design from the following aspects. First, this trial meets the methodological demand for adequate randomization, allocation concealment, and blinding of patients, outcome assessors, and statisticians. Second, patients will be provided 3 treatment sessions per week in the 4-week treatment phase, giving a total of 12 sessions. Compared with “6 treatment sessions over 3 weeks” in a previous study, the “dose” of acupuncture in our trial is more sufficient, which has been well practiced in clinical practice of China [30].

According to the TCM definition of IBS: “suppressed emotions and concerns would induce a liver qi stagnation, which in turn would lead to an attack of the liver on the spleen and stomach. The resulting weakness of the spleen leads to digestion problems. Furthermore, liver qi stagnation would block qi flow in the meridians, which would induce abdominal pain” [31, 32], the liver is an important organ related to IBS. Most IBS patients are accompanied by abnormalities of mood, such as anxiety, depression, and tension, which is in line with the clinical manifestations of liver dysfunction. The main symptoms of IBS are abdominal pain, constipation, and fatigue, which are common manifestations of spleen deficiency syndrome. Therefore, the additional specific acupoints in this trial were selected in accordance with the TCM treatment principles of invigorating the spleen and regulating the liver.

This study still has some noteworthy limitations. First of all, the acupuncturists cannot be blinded due to the nature of the acupuncture intervention. Second, when patients are unsatisfied with the treatment or cannot tolerate the symptoms of IBS, they may prefer to other treatment, which will increase the drop-out rate. In order to give patients a more comprehensive understanding of the trial, we have trained researchers to establish a good communication relationship with patients. Third, the follow-up of 8 weeks is short, which may affect the outcomes of this trial. We will conduct the large-scale trials with long-termfollow-up of patients.

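### Missing outcomes may be filled by LOCF or by multiple imputation with no rule between them, so LOCF can be the primary analysis, and no planned analysis tests the missing-data assumption

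*Protocol article*

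**What the plan says.** The Analytical methods section sets the analysis population: "Intention-to-treat (ITT) set will be used in all efficacy analysis, which will consist of all patients who have been randomized into groups". It then states that "the missing outcome data will be complemented using last observation carried forward (LOCF) or multiple imputation". It does not say which of the two is primary, which outcome or visit each serves, or what would decide between them.

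The visits at stake are in the Outcomes section. "The primary outcome is the response rate of week 4 after randomization", and for the secondary time points "The response rate will also be measured at weeks 1, 2, 3, 8, and 12 after randomization". The Abstract gives the timing of treatment: "All patients will be treated with acupuncture 12 times within 4 weeks and followed up for 8 weeks". Weeks 8 and 12 therefore fall after needling has stopped.

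The Discussion names an expected cause of loss: "when patients are unsatisfied with the treatment or cannot tolerate the symptoms of IBS, they may prefer to other treatment", which it says will raise drop-out. The Data management section plans to collect data by telephone from patients who discontinue or deviate, if they are willing.

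One sensitivity analysis is stated: "A per-protocol analysis will be used for primary outcome as sensitivity analysis covering patients who complete ≥ 10 sessions and have no major protocol violations".

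**The concern.** The two methods rest on different assumptions. LOCF holds a patient's status fixed from the last observation onward. Multiple imputation predicts the missing value from observed data and carries the uncertainty of that prediction into the standard error. Joining them with *or* leaves a single-imputation method available as the primary analysis of the primary outcome.

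The no-change assumption is hard to defend here for two reasons found in the document. Loss is expected to be related to symptoms and satisfaction, that is, to the outcome. And the follow-up visits exist to show whether response lasts once treatment ends, whereas LOCF settles that question by assumption for every patient lost before them.

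At stake are the week-4 response rates, the week-8 and week-12 rates, and their p-values. The Sample size section says the results will help to size a later trial, so an error in the response rates would carry over into it.

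**Working it through.** **1. Inputs in the document.** The stated sample size reproduces: 3 arms × 30 = 90. The article gives no drop-out rate and no expected response rate, so everything numerical below is illustration on assumed inputs.

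**2. What LOCF inserts.**
- Week 4 missing: the status at week 3, 2 or 1, partway through the course.
- Week 8 missing: the status at week 4 or earlier, from the treatment period.
- Week 12 missing: the week-8 status if there is one, otherwise a status from the treatment period.

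**3. Bias in one arm, general form.** Let d be the share missing, q the share of those missing whose last observed status was a response, and t the share of them who are truly responders at the target visit. Then

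bias = d × (q − t).

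Assumed ranges: d = 5-20%, q = 20-60%, t = 0-20%.
- Smallest: q = t = 20% gives 0 points.
- Middle: 0.10 × (0.40 − 0) = 0.04, or 4 points, which is 0.04 × 30 = 1.2 patients.
- Largest: 0.20 × (0.60 − 0) = 0.12, or 12 points, which is 3.6 patients.
- If every leaver was a non-responder when last seen (q = 0), the bias is −d × t. With d = 20% and t = 20% that is −4 points. The sign therefore depends on who leaves.

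**4. Week 12, with the week-4 status carried forward.** Let m be the share missing after week 4, p4 the week-4 response and p12 the true week-12 response. If missingness is independent of response and relapse,

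LOCF rate = (1 − m) × p12 + m × p4, so bias = m × (p4 − p12).

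With p4 = 50% assumed:

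| m | p12 | LOCF rate | Bias (points) |
|---|---|---|---|
| 10% | 40% | 41% | 1 |
| 10% | 30% | 32% | 2 |
| 30% | 40% | 43% | 3 |
| 30% | 30% | 36% | 6 |

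**5. What one patient can do at 30 per arm.** Chi-square test, assumed counts:

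| Responders of 30 | p, uncorrected | p, continuity-corrected |
|---|---|---|
| 15 v 8 | 0.063 | 0.111 |
| 16 v 8 | 0.035 | 0.065 |
| 17 v 8 | 0.018 | 0.036 |

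One reclassified patient crosses the stated 0.05 level between the first two rows without correction, and between the last two with it. Shifts of one or two patients lie within the illustration in step 3.

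**6. Whether the per-protocol analysis covers this.** It selects patients by sessions completed and absence of major violations. That changes who is analysed, not what is assumed about missing values. It is also stated for the primary outcome only, so weeks 8 and 12 have no sensitivity analysis at all.

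**The case against.** The strongest reply concerns direction. A reader might infer that LOCF flatters acupuncture or overstates how long its effect lasts. The document does not support that. Patients who leave dissatisfied or with intolerable symptoms are likely to be non-responders when last seen, and LOCF then carries non-response forward. The week-12 figures in step 4 assume instead that leavers resemble the whole arm; they also concern one arm at a secondary time point. A bias of similar size in each arm would partly cancel in the comparison. All of this stands, and it limits what can be claimed about size and sign.

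A reader might also infer that the open wording lets the preferred result be chosen. The Blinding and Analytical methods sections have blinded statisticians do the analysis, and allocation is not revealed until it is finished. This reduces the risk, though coded arms still produce p-values. Telephone retrieval reduces missingness, but only among willing patients.

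Nor does the plan promise confidence intervals, so the single-imputation objection applies to standard errors and p-values, not to a stated interval.

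Finally, a condensed article may leave the method for each outcome to an analysis plan that is not shown. That would answer a complaint about missing detail. It does not answer this point, because the article itself names LOCF as acceptable, and an analysis plan that made it primary would comply fully.

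**Conclusion.** The point holds in a limited form. The wording permits an LOCF primary analysis that rests on a no-change assumption, in a trial that expects outcome-related drop-out and measures response for 8 weeks after treatment ends. LOCF also leaves imputation uncertainty out of the standard errors and p-values. No planned analysis tests the missing-data assumption.

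The document does not fix the size or direction of any bias. The 1 to 6 points at week 12 rest wholly on the assumed response rates and on missingness independent of relapse; other assumptions give zero or a negative bias. It would be wrong to conclude that the trial will overstate the benefit of acupuncture.

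The exploratory pilot setting lowers the consequence but does not remove it, because the trial tests at 0.05 and is meant to inform the size of a later one. The wording should be changed; it is not a fatal defect.

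**What to change.** Before unblinding, amend the missing-data sentence as follows.

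- **One primary method.** Name multiple imputation. Include treatment arm, baseline pain, baseline loose-stool days and a parsimonious set of weekly diary values. Impute pain and loose-stool days, then derive response from them. Use one model with arm as a term: two components at baseline and six visits make 2 × 7 = 14 correlated variables, which may be unstable if imputed separately in arms of 30.
- **LOCF.** Remove it as a primary option. Keep it at most as a labelled sensitivity analysis.
- **A test of the assumption.** Add a sensitivity analysis that counts missing response as non-response in all arms, at week 4 and also at weeks 8 and 12. Standard multiple imputation assumes that data are missing at random, so by itself it does not settle outcome-related drop-out.

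The cost is protocol or analysis-plan wording, light programming, and standard errors slightly larger than LOCF would report. No additional patients, visits or data are needed.

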### Interventions

Before acupuncture treatment, licensed acupuncturists with at least 3 years of acupuncture experience will be trained in how to locate acupoints and non-acupoints, puncture and manipulate needles. All acupoints are localized according to the WHO Standard. Single-use sterile needles (0.30 mm in diameter and 30 mm in length or 0.30 mm in diameter and 25 mm in length; Hwato, Suzhou, China) will be used in the SA group and NSA group. To help maximize blinding of patients in the NA group, a blunt-tipped placebo needle will be used (similar to the Streitberger design [21]) which can provide patient-blinding effects with a similar appearance to conventional needles but no skin penetration [22]. And adhesive pads will be used in each group. Each patient will be scheduled to undergo 12 sessions of treatment, with each acupuncture lasting 30 min for 4 weeks (three sessions per week, every other day ideally). During the trial, patients will not be allowed to use other therapies or medications that have a therapeutic effect on IBS, such as traditional Chinese medicine (TCM) or proprietary Chinese medicine, antidiarrheal, antispasmodic, intestinal antibiotics, probiotics, and so on. Loperamide (Imodium, Xian Janssen Pharmaceutical Ltd., China) will be used as rescue medication under the guidance of gastroenterologists whenever necessary. The medication status and other non-irritable bowel syndrome drug applications of patients will be strictly recorded during the trial.

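### The per-protocol set for the week-4 primary outcome has no week-4 cut-off for drug violations, so drug use in weeks 5–12 can exclude valid week-4 results

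*Protocol article*

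**What the plan says.** The Primary outcome section sets a single time point: "The primary outcome is the response rate of week 4 after randomization". The Abstract gives the length of the trial: "All patients will be treated with acupuncture 12 times within 4 weeks and followed up for 8 weeks". Response is assessed again after the primary time point: "The response rate will also be measured at weeks 1, 2, 3, 8, and 12 after randomization".

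The Analytical methods section gives the main analysis set, "Intention-to-treat (ITT) set will be used in all efficacy analysis, which will consist of all patients who have been randomized into groups", and then adds: "A per-protocol analysis will be used for primary outcome as sensitivity analysis". That second set covers "patients who complete ≥ 10 sessions and have no major protocol violations (taking other drugs during the trial, etc". Taking other drugs is the only example of a major violation given, and the period attached to it is the whole trial.

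The ban that this refers to, in Interventions, has the same span: "During the trial, patients will not be allowed to use other therapies or medications that have a therapeutic effect on IBS". The same section permits loperamide as rescue medication and requires medication use to be recorded.

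**The concern.** A per-protocol set for a week-4 outcome should depend on what happened up to week 4. The session criterion does, because all 12 sessions fall within the first 4 weeks. The drug criterion does not. A patient with 12 sessions, no other drug through week 4 and a complete week-4 diary could be removed because of a drug taken in week 9.

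Such an exclusion says nothing about adherence in the period being analysed, and it may depend on the outcome itself. The Discussion expects that "when patients are unsatisfied with the treatment or cannot tolerate the symptoms of IBS, they may prefer to other treatment". If patients who failed at week 4 are the ones who later take something else, the rule removes failures and keeps responders.

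This is the only analysis that the protocol calls a sensitivity analysis of the primary outcome. Its job is to support or challenge the intention-to-treat result, and a set selected on later events does that job poorly.

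**Working it through.** **1. What the protocol fixes.** There are three arms of 30, so 3 × 30 = 90, as the Sample size section states. It gives no response rate and no rate of drug use after week 4, so every rate below is an assumption, shown over a range.

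**2. What the period means.** The drug ban in Interventions and the monitoring in Adverse events use the same trial-long wording. Where the authors mean the treatment weeks they have narrower terms: Blinding speaks of the treatment and the Discussion of a 4-week treatment phase. The per-protocol definition uses neither. The natural reading is therefore 4 + 8 = 12 weeks.

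**3. Formula.** Let p be the true week-4 response rate, r the share of week-4 responders who take another drug in weeks 5–12, and f the same share among failures. Under the rule as written:

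- retained fraction = p(1−r) + (1−p)(1−f)
- per-protocol rate = p(1−r) / [p(1−r) + (1−p)(1−f)]

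Equivalently, the response odds are multiplied by (1−r)/(1−f).

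**4. One arm, p = 0.40, r = 0.05.**

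| f | Calculation | Per-protocol rate | Excluded |
|---|---|---|---|
| 0.20 | 0.38 / (0.38 + 0.48) | 44.2% | 14% |
| 0.30 | 0.38 / (0.38 + 0.42) | 47.5% | 20% |
| 0.40 | 0.38 / (0.38 + 0.36) | 51.4% | 26% |

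In whole patients: 12 responders of 30 is 40%. If 6 of the 18 failures and no responders take a drug later, the rate becomes 12/24 = 50%.

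**5. When the bias vanishes or reverses.** If f = r, the odds factor is 1 and the rate does not change. If p = 0.40, f = 0.10 and r = 0.30, the rate is 0.28 / (0.28 + 0.54) = 34.1%, a fall of 5.9 points.

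**6. Two arms.**

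| True rates | f in each arm | r | Per-protocol rates | Difference: true → per-protocol (points) |
|---|---|---|---|---|
| 50% v 30% | 0.30 v 0.30 | 0 | 58.8% v 38.0% | 20 → 20.8 |
| 50% v 30% | 0.30 v 0.10 | 0 | 58.8% v 32.3% | 20 → 26.6 |
| 50% v 30% | 0.20 v 0.40 | 0.05 | 54.3% v 40.4% | 20 → 13.9 |
| 40% v 40% | 0.20 v 0.40 | 0.05 | 44.2% v 51.4% | 0 → −7.2 |

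If r and f are the same in both arms, both odds are multiplied by the same factor. The unadjusted odds ratio is then unchanged and the difference in rates moves little. If uptake differs by arm, the difference can move either way.

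**7. With the window closed at week 4.** Drug use in weeks 5–12 removes no one, so this bias is zero for any f and r.

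**The case against.** Four points can fairly be made against this.

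- The operative word is major, and the bracket is an open-ended example. Whether a week-9 drug is a major violation for a week-4 outcome could be decided in a fuller document. This stands in part: such a document could narrow the rule, and the text does not prove that anyone will be excluded this way. But drug-taking is the one example named, its period is stated, and that period is wrong for a week-4 endpoint. This is a rule fixed badly, not a detail left out.
- A reader might infer that the Discussion itself says failures will be the patients excluded. It does not. The sentence goes on to say that turning to other treatment will raise drop-out, and it gives no timing. Some of those patients may leave early and miss the session criterion anyway. Higher later uptake among failures is plausible from it, no more.
- A reader might infer that the rule inflates the response rate in every arm. That needs f greater than r. Step 5 shows no bias when they are equal and a fall when the order is reversed.
- The stakes are limited. With 30 per arm and a 40% rate, the standard error of a difference is √(2 × 0.24/30), about 13 points, so a 7-point distortion is roughly half a standard error. That distortion also needs an assumed imbalance between arms. A reader might fear that inflated rates would be used to size the large trial, but the Sample size section refers only to the results of the study and does not say that per-protocol rates will be used.

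**Conclusion.** The point holds as a defect in the definition of the per-protocol set. As written, drug use after the endpoint can exclude patients whose week-4 result is valid and cannot have been affected by it. With a true rate of 40% and later uptake of 5% in responders and 20–40% in failures, the per-protocol rate would read 44–51%, and 14–26% of patients would be lost. These uptake figures are assumptions; the protocol supports the direction only as plausible. A material distortion of the comparison between arms needs uptake that differs by arm, and its sign is not predictable.

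The intention-to-treat analysis of all randomized patients is untouched, so the documents do not support a claim that the main result is biased. The wording should be corrected because the sensitivity analysis is otherwise hard to interpret and the correction is nearly free.

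**What to change.** In Analytical methods, add one sentence: for the per-protocol set of the week-4 primary outcome, only violations occurring from randomization to the end of the week-4 diary week count. No rule is needed for weeks 8 and 12, because the per-protocol analysis is planned for the primary outcome only.

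Interventions and Analytical methods should also be reconciled on whether the permitted rescue medication counts as another drug for this purpose. At present it is allowed in one section and possibly a ground for exclusion in the other.

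The cost is a line of text. Medication use is already to be recorded, though the dates of use must be available to apply the window. No extra patients are needed, and the per-protocol set can only stay the same or grow; under the assumptions above it regains about 4 to 8 patients per arm of 30 (0.14 × 30 = 4.2; 0.26 × 30 = 7.8). The change does not remove selection through drug use within weeks 1–4. That is inherent in a per-protocol analysis and should be borne in mind when it is read.

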### Adverse events

During the trial, adverse events will be monitored and recorded in the form of a specific questionnaire by patients, outcome assessors, and acupuncturists. Based on the potential relationship between the needling procedure and adverse events, acupuncturists and related specialists will categorize all adverse events as treatment-related or not within 24 h of occurrence. Common acupuncture-related adverse events consist of dizziness, subcutaneous hematoma, continuous post-needling pain, local bleeding, itching at the sites of needle insertion, and so on.

